#### Implementation

An independent randomization system account is created for investigators at each study site for the randomization implementation. Each investigator will log in to the system via a website to enter the randomization page, input the information of the participants, check the name and code of the study site, and confirm the randomization information. Then, the randomization code and allocated arm of the participant will be generated in the system background which is blinded for the investigators. Additionally, the operator at each study site will log in to the system using an independent account with the authority to view the allocated arms. At this time, the participants are successfully enrolled in this study.

#### Blinding

Study participants and all staff, including investigators, clinical care providers, statisticians, and personnel who recruit, follow-up with participants, and collect data are blinded to the randomizations. The operators will be unblinded to implement the PFM procedure and required to keep blinded to all other staff. After completing the procedure, we will ask about the participants’ feelings or any discomforts and if they can tell the real intervention and sham intervention. Once severe adverse events (SAE) that might be related to the PFM procedure occur, the principal investigators will be able to disclose the arm allocation. The disclosure reason, date, and location will be recorded in detail.

## Methods: data collection, management, and analysis

### Data collection

The outcomes will be assessed at baseline, 1 day, 14 days, 30 days, and 90 days after the intervention. All staff involved in the collection of data were trained by the standard operating procedure of the study. The data will be recorded utilizing electronic CRFs and EDC systems.

### Baseline data collection

The following measures will be completed at baseline.• Written informed consent• Clinical questionnaire• Office BP and 24-h ambulatory BP• Anthropometric information including height, weight, waist circumference, and hip circumference• Electrocardiography and cardiac ultrasound• Arteries stiffness assessments (PWV)• Imaging examinations including ultrasonic examinations of renal and perirenal fat, carotid ultrasound, and magnetic resonance imaging for perirenal fat and hypothalamic function• Blood tests including routine blood tests, blood biochemical tests, and C-reactive protein• Urine tests including routine urine tests, urine biomarkers of acute renal injury (Ngal, TIMP2, IGFBP7)• Hypertensive drug concentration detection (serum and urine)

### Data collection at 1 day after intervention

• Office BP and 24-h ambulatory BP• Electrocardiography• Arteries stiffness assessments (PWV)• Imaging examinations including ultrasonic examinations of renal and perirenal fat and carotid ultrasound• Blood tests including routine blood tests, blood biochemical tests, and C-reactive protein• Urine tests including routine urine tests and urine biomarkers of acute renal injury (Ngal, TIMP2, IGFBP7)

### Data collection at 14 days after intervention

• Office BP

### Data collection at 30 days after intervention

• Office BP and 24-h ambulatory BP• Anthropometric information including height, weight, waist circumference, and hip circumference• Electrocardiography• Arteries stiffness assessments (PWV)• Imaging examinations including ultrasonic examinations of renal and perirenal fat, carotid ultrasound, and magnetic resonance imaging for perirenal fat and hypothalamic function• Blood tests including routine blood tests, and biochemical blood tests• Urine tests including routine urine tests• Hypertensive drug concentration detection (serum and urine)

### Data collection at the final visit

• Office BP and 24-hour ambulatory BP• Anthropometric information including height, weight, waist circumference, and hip circumference• Electrocardiography• Arteries stiffness assessments (PWV)• Imaging examinations including ultrasonic examinations of renal and perirenal fat, carotid ultrasound, and magnetic resonance imaging for perirenal fat and hypothalamic function• Blood tests including routine blood tests, and biochemical blood tests• Urine tests including routine urine tests• Hypertensive drug concentration detection (serum and urine)

All the eligible participants will have comprehensive health examinations and receive PFM therapy or sham-procedure for free. They will have close relationships with physicians who can provide professional consultations and medication guidance for their health problems. Traffic and accommodation subsidies will provide for all participants to promote participant retention and complete follow-up. If participants discontinue follow-up, the reasons will be recorded in detail, and their clinical treatment and other rights shall not be affected.

### Data management

Study data will be recorded via the Electronic Data Capture (EDC) system (Nanjing Yike Valtai Information Technology Co., Ltd). Well-trained practitioners will log into the website and input data. The EDC system has the function of automatically checking data format, rules, and range so as to ensure the accuracy of data. Moreover, manual reconfirmation by a third staff is also required. Any change in data recording is permitted and tracked with reasons and dates in the EDC system. Additionally, data quality will be under the supervision of a third party. All documents and data will be stored at the institutional office of each study site.

### Statistical method

For the primary endpoint, a mixed-effect model for repeated measures (MMRM) adjusted with baseline office SBP will be used to compare the group difference of the office SBP changes from baseline to 1 month. For the secondary endpoint, we will also use the MMRM method adjusted with mean SBP or heart rate to assess the changes in the mean SBP or heart rate from baseline to each visit point. And LS-means method adjusted with baseline SBP or heart rate will be used to estimate the changes in SBP or heart rate and 95% confidence intervals. Imputation for missing values of the main indicator will be conducted using the Markov chain Monte Carlo (MCMC) model which will be performed as the result of the sensitive analysis. We predefine an adverse event of laboratory index that is significantly abnormal at follow-up compared with baseline. Detailed presentation of adverse events will be described and explore the relationship with PFM products. The efficacy analyses will be carried out based on the full analysis set and the pre-protocol set. All baseline characteristics analysis will be conducted on the basis of the full analysis set. The safety evaluation will be analyzed from the safety analysis set. A two-sided *P* < 0.05 will indicate significance in all statistical analyses used by the SAS software V.9.4 (SAS Institute, Cary, NC).

An interim analysis is planned when 50 subjects (100 subjects in total) are enrolled in each group and completed 1 month follow-up, which will be conducted by an independent data monitoring committee (IDMC). The purposes of the interim analysis are as follows: (1) to evaluate the safety (a necessary disruption of the study is considered when there are serious or expected adverse events) and (2) to assess the efficacy. This trial will be expected to terminate in advance if the hypothesis test *P* value is less than the boundary value of the interim analyzed *α* for the primary endpoint. And if the *P* value is greater than interim analyzed *α* with statistical power less than 60%, re-estimating the sample size is needed to make the final statistical power greater than 80%. In accordance with O’Brien-Fleming method, the interim analyzed *α* = 0.005, and final *α* = 0.048.

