### Eligibility criteria

The inclusive criteria are as follows:• Individuals aged 18–65 years old• Individuals have uncontrolled BP when receiving a medication regimen of one, two, or three antihypertensive medication classes for at least 4 weeks; and uncontrolled BP is defined as office systolic blood pressure (SBP) ≥ 140 mmHg and < 180 mmHg, and 24-h ambulatory BP monitoring (ABPM) average SBP ≥ 135 mmHg, regardless of diastolic BP• Individuals have at least 20 mm in the anteroposterior, transverse, and axial diameters of inferior perirenal fat measured by ultrasound• Individuals are willing to sign the informed consent of the study

The exclusive criteria are as follows:• Individuals are diagnosed with secondary hypertension (e.g., renal parenchymal hypertension, renal artery stenosis, primary aldosteronism, pheochromocytoma, Cushing’s syndrome, aortic coarctation, severe obstructive sleep apnea-hypopnea syndrome)• Individuals have a history of kidney and or kidney surrounding tissue surgery• Individuals have impairment of liver or kidney function (ALT, AST, or creatinine is greater than 3 times the upper limit of normal reference)• Individuals have a myocardial infarction, unstable angina pectoris, cerebrovascular accident, or transient ischemic attack within 6 months before enrollment• Individuals have type 1 diabetes or poorly-controlled type 2 diabetes• Individuals have uncontrolled thyroid dysfunction• Individuals have urinary calculi and/or hematuria• Individuals have atrial fibrillation• Individuals have severe structural heart disease (e.g., heart valve disease, cardiomyopathy, congenital heart disease)• Individuals have second-degree and above atrioventricular block• Individuals have abnormal coagulation function• Individuals have infected waist skin• Individuals have a malignant tumor• Individuals are pregnant, nursing, or planning to be pregnant• Individuals are unwilling to sign informed consent• Individuals fail to complete the screening period

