### Outcomes

We speculate that PFM will have a significant blood pressure lowering effects compared with the sham-control group. The endpoints in the present study include primary endpoints, secondary endpoints, and safety endpoints.

Primary endpoint measure:• Changes in office systolic blood pressure at 1-month compared with baseline

Secondary outcome measures:• Changes in office blood pressure at 3 months compared with baseline• Changes in mean systolic blood pressure measured by 24-h ambulatory blood pressure monitoring at 1 month compared with baseline• Changes in mean systolic blood pressure measured by 24-h ambulatory blood pressure monitoring at 3 months compared with baseline• Changes in the heart rate at 1 month compared with baseline• Changes in the mean heart rate measured by 24-h ambulatory blood pressure monitoring at 1 month compared with baseline

Safety endpoint measures:• Any severe adverse events (SAE) related to the intervention. The SAE was defined as acute renal failure, acute intestinal perforation, and thromboembolic events, etc.

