### Sample size

The PASS software (version 2011) was used to calculate the sample size. This study is a parallel group design, whose primary endpoint is the difference in office BP at 1 month compared with baseline. Our previous pilot study was a single-arm design recruiting 15 participants with mild-moderate hypertension for PFM therapy with results unpublished. Based on the outcome of the pilot study, the mean change in office SBP from baseline to 1 month was expected to 10 mmHg with a deviation of 13 mmHg in the PFM group. Meanwhile, we assumed that a mean difference of office SBP was 5 mmHg [15, 16] with a deviation of 13 mmHg in the sham control group. The sample size was calculated as 100 in each group with a power of 80%, a two-sided significance level of 5%, and a drop-out rate of 15%.

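### The primary MMRM could also adjust for baseline 24-h mean SBP, which every participant has by entry rule: an optional, small gain in precision, not the correction of an error

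*Protocol article*

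**What the plan says.** - **Primary model** (Protocol article, Statistical method): "a mixed-effect model for repeated measures (MMRM) adjusted with baseline office SBP will be used to compare the group difference". Baseline office SBP is the only covariate named. The section does not say that it is the only term in the model.
- **Primary endpoint** (Outcomes): "Changes in office systolic blood pressure at 1-month compared with baseline".
- **Entry rule** (Eligibility criteria): office SBP of at least 140 and below 180 mmHg, together with "24-h ambulatory BP monitoring (ABPM) average SBP ≥ 135 mmHg".
- **Baseline assessments** (Baseline data collection): "Office BP and 24-h ambulatory BP". Table 1 also schedules the ambulatory measurement in the screening period.
- **Planning assumptions** (Sample size): the change in the treated arm "was expected to 10 mmHg with a deviation of 13 mmHg in the PFM group"; for sham, "we assumed that a mean difference of office SBP was 5 mmHg" "with a deviation of 13 mmHg in the sham control group"; and "a power of 80%, a two-sided significance level of 5%, and a drop-out rate of 15" per cent. The stated result is 100 per group.
- **Interim look** (Statistical method): one efficacy look by the IDMC when 50 per group have completed one month, with alpha 0.005 at the interim and 0.048 at the end.

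**The concern.** Baseline office SBP is at once the selection variable, the baseline of the outcome and the only named covariate. Selecting on a noisy reading brings regression to the mean. Two participants with the same office reading may differ in usual pressure, and the one whose ambulatory mean is lower may plausibly fall further by Day 30 in either arm. A second, separately obtained baseline pressure can help predict that fall, and the stated model does not use it.

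What is at stake is precision. Any variance in Day-30 office SBP that baseline 24-h SBP could explain stays in the residual and widens the confidence interval of the primary comparison. The trial has no spare power, and its interim rules turn on the primary P value and on power, so even a small gain at almost no cost is worth considering.

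**Working it through.** **1. The plan's own figure.** Inputs from Sample size: difference 10 − 5 = 5 mmHg, SD 13 mmHg, two-sided 5%, power 80%, drop-out 15%.

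n per arm = 2 × (13/5)² × (1.960 + 0.842)² = 106.1, so 107. After drop-out, 107 / 0.85 = 125.9, so **126 per arm** (128 with the t distribution). The stated 100 is not reproduced. A one-sided 5% test would give 84 / 0.85 = 98.8, so 99 (100 with the t distribution), but the text says two-sided.

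**2. Power as planned.** 100 × 0.85 = 85 evaluable per arm. The noncentrality is 5 / (13 × √(2/85)) = 2.507, and power is Φ(2.507 − 1.960) = **70.8%** (70.2% at the final alpha of 0.048).

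**3. How much variance the covariate could remove.** The documents give no correlation between baseline 24-h SBP and later office SBP, so this rests on assumptions:
- true office SBP has an SD of 10 to 16 mmHg;
- true office and ambulatory SBP correlate at 0.5 to 0.8;
- ambulatory error has an SD of 5 to 8 mmHg;
- population means are 148 (office) and 138 (ambulatory) mmHg;
- the SD of change before selection is 13 mmHg, with either all or half of its variance being office measurement error and the rest genuine change over 30 days.

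Both entry cut-offs were applied to simulated participants. Day-30 office SBP was then regressed on baseline office SBP, with and without baseline 24-h SBP. This single-visit regression stands in for the Day-30 contrast of the MMRM.

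| Share of change variance that is measurement error | Further residual variance removed |
|---|---|
| 100% (office error SD 13/√2 = 9.19) | about 1% to 7% |
| 50% | about 0.3% to 2.6% |

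**4. What that is worth.** Treat 13 mmHg as the residual SD before the extra covariate. If a fraction v of the variance is removed, the residual SD becomes 13 × √(1 − v). With 85 per arm and two-sided 5%:

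| v | Residual SD | Noncentrality | Power | Gain | Equivalent extra evaluable participants, 170 × (1/(1 − v) − 1) |
|---|---|---|---|---|---|
| 0 | 13.00 | 2.507 | 70.8% | – | – |
| 0.003 | 12.98 | 2.511 | 70.9% | 0.1 points | 0.5 |
| 0.07 | 12.54 | 2.600 | 73.9% | 3.1 points | 12.8 |

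**5. If 13 mmHg is the SD of the raw change instead.** Adjusting for baseline office SBP then already lowers the residual SD. In one scenario (true SD 13, correlation 0.65, ambulatory error SD 5, all change variance being error) it is 11.67 without and 11.47 with the extra covariate, a variance reduction of 1 − (11.47/11.67)² = 3.4%. At alpha 0.048, power goes from 79.3% to 80.6%. The starting level differs from step 4, but the gain is again small.

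**6. What it would take to reach 80%.** With 85 per arm, 80% power needs a residual SD of 5 / (√(2/85) × 2.802) = 11.63. From 13, that means removing 1 − (11.63/13)² = 20% of residual variance, a partial correlation of about 0.45. This is almost three times the top of the range in step 3.

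**The case against.** - **The stated model is not wrong.** Adjusting a change from baseline for its own baseline is standard, and it is unbiased under randomisation. A chance imbalance in 24-h SBP is not bias, because the confidence interval already allows for it. This stands in full.
- **A condensed article may leave covariates to the SAP.** The section lists neither visit nor centre terms, and an unseen SAP could add the covariate. This also stands, and it is a reason to treat the point as optional.
- **The gain is small and rests on assumptions.** This stands. If half of the change variance is genuine change, the gain is about 1 power point at most. Entry also truncates ambulatory SBP from below, which limits what it can explain.
- **It is not quite free.** Recruitment had begun, with 74 participants recruited by February 2022, and Ethics and dissemination requires ethics permission for amendments. The cost is low but not nil.

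Readers might also infer two stronger things. The first is that this covariate lifts a trial with a thin margin over 80% power. The documents do not support that: the 79.3% to 80.6% scenario starts from a residual SD of 11.67 that appears nowhere in them, and on the planning SD the start is about 70%.

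The second is that gains of 7 points or more are likely. A sketch in which office and ambulatory pressure share one true value does give partial correlations of about 0.2 to 0.5. That amounts to assuming that the two true pressures correlate perfectly, for which the documents offer no basis.

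**Conclusion.** The point holds as an optional efficiency gain. The protocol article names only baseline office SBP, while a second relevant baseline pressure is available for every participant through the entry rule. Adding it would remove roughly 0.3% to 7% of residual variance, worth about 0.1 to 3 power points at 85 evaluable per arm. Those figures depend on the assumptions in the working, none of which the documents supply. The direction of the gain is plausible, but its size is uncertain and small.

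The covariate leaves the sample-size problem in place. The stated inputs need about 126 per arm, and 100 per arm gives about 70% power after drop-out. That is a separate and larger matter.

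**What to change.** In Statistical method, state that the primary MMRM is adjusted for baseline office SBP and baseline 24-h mean SBP. Fix this before the interim comparison, since that look already compares the arms on the primary endpoint, and use the same model unchanged at the interim and the final analysis.

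The cost is one model degree of freedom (or one per visit if the covariate interacts with visit) and a minor amendment with ethics permission. No new data and no extra participant burden are involved.

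Separately, correct the Sample size section so that its inputs, its sidedness and the number per arm agree.

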### Criteria for discontinuing

Participants may discontinue this trial for any of the following reasons:• They may choose to withdraw for any reason• They have severe side effects that require unmarking to get cured• Their blood pressure is within “escape criteria,” defined as office SBP ≥ 180mmHg or < 90 mmHg• They have a significant deviation from the study algorithm, e.g., changing the established antihypertensive drugs scheme• Any other rational reasons to withdraw from the study

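### The one missing-data sensitivity analysis named in the article (MCMC imputation) makes the same missing-at-random assumption as the primary MMRM, so agreement between them would not show robustness to it

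*Protocol article*

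**What the plan says.** All the relevant text is in the protocol article.

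- **Primary analysis (Statistical method).** "a mixed-effect model for repeated measures (MMRM) adjusted with baseline office SBP will be used to compare the group difference" of the change in office SBP from baseline to 1 month.
- **Missing data (same section).** "Imputation for missing values of the main indicator will be conducted using the Markov chain Monte Carlo (MCMC) model", and its role is given as "which will be performed as the result of the sensitive analysis". The section names no other missing-data analysis. It does not state a missingness assumption, and it describes no shift, reference-arm or tipping-point element in the imputation.
- **Analysis sets (same section).** "The efficacy analyses will be carried out based on the full analysis set and the pre-protocol set". This changes the population analysed, not the assumption about the unobserved values.
- **Expected loss (Sample size).** The calculation allows for "a drop-out rate of 15" per cent.
- **Reasons for leaving (Criteria for discontinuing).** Participants may leave by own choice, for severe side effects, for office SBP outside set limits, or because "They have a significant deviation from the study algorithm, e.g., changing the established antihypertensive drugs scheme".

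**The concern.** A sensitivity analysis for missing data should change the assumption that the primary analysis cannot verify. MMRM is likelihood-based and valid when missingness depends only on observed data. Standard MCMC multiple imputation draws the missing values from a multivariate normal model fitted to the observed data, under the same condition. Given the same visits, the two estimate the same quantity apart from simulation noise. If unobserved outcomes differ systematically from what the observed visits predict, both are wrong by the same amount and still agree.

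At stake is how the primary result is read. The article specifies a formal two-sided test with an early efficacy stop. Agreement between MMRM and MCMC could be taken as evidence that drop-out does not matter, although that question was not put to the data.

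**Working it through.** **1. The plan's own figures.** The point does not rest on a stated result. The one figure it uses is the drop-out allowance: 100 per group × (1 − 0.15) = 85 completers per group. (The 100 per group does not follow from the stated two-sided 5% inputs, but that is a separate matter and does not bear on this point.)

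**2. Do the two methods separate when missing at random fails?** This was checked by simulation. The assumptions below are not from the documents unless marked:

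- four correlated visits, correlation 0.5, no separate baseline covariate;
- SD 13, 100 per arm and mean changes of −10 and −5 mmHg (Sample size section);
- about 15% missing from the third visit on, with sham-arm loss unrelated to outcome;
- 200 runs.

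A maximum-likelihood repeated-measures normal model (standing in for the MMRM) was compared with multivariate-normal MCMC imputation.

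| PFM-arm drop-out depends on | Bias vs full data, likelihood | Bias vs full data, MCMC | Mean absolute gap per run |
|---|---|---|---|
| the observed earlier visit (missing at random) | −0.03 | −0.03 | 0.13 mmHg |
| the unobserved 1-month value, poor responders lost more often | −1.51 | −1.51 | 0.11 mmHg |

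The Monte Carlo standard error of each bias is about 0.05. In the second row both methods overstate the effect by 1.51 / 5 = about 30%, yet they agree as closely as in the first row. The 1.51 follows from the chosen mechanism and is not a forecast for this trial. The finding is that the gap between the methods does not react.

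**3. What a tipping-point analysis would report.** Inputs: SD 13 (Sample size), 85 completers per arm (step 1), final alpha 0.048 (Statistical method), and an observed effect of 10 − 5 = 5 mmHg, the planned difference.

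- SE = 13 × √(2/85) = 1.99 mmHg.
- Smallest significant effect = 1.977 × 1.994 = 3.94 mmHg (normal critical value).
- If the 15% missing PFM values are worse by delta than imputed, effect = 5 − 0.15 × delta.
- Tipping delta = (5 − 3.94) / 0.15 = about 7.0 mmHg (about 6.9 with the t critical value on 168 degrees of freedom; about 7.3 at alpha 0.05 with the normal value).

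| Delta (mmHg) | Effect (mmHg) | Below 3.94? |
|---|---|---|
| 2.5 | 4.63 | no |
| 5 | 4.25 | no |
| 10 | 3.50 | yes |

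A smaller observed effect tips sooner: at 4.5 mmHg, (4.5 − 3.94) / 0.15 = about 3.7 mmHg. The SE is held at 1.99 throughout, as an approximation; an actual multiple-imputation analysis would re-estimate it.

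**The case against.** **The article is not the full plan.** It condenses the protocol, and tipping-point or reference-based analyses are often specified only in an analysis plan. This stands as a limit: the MCMC run is the only such analysis in this article, not necessarily in the trial. It does not remove the point, because the article does specify the sensitivity analysis and chooses one that cannot test the assumption. If the fuller plan already contains a departure from missing at random, confirming that settles the matter.

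**Missing at random may be reasonable here.** A reader might infer that the blood-pressure escape rule makes it untenable. The documents do not support that. The trigger is office SBP itself, the primary outcome variable, and if the reading is taken at a scheduled visit and enters the MMRM, the exit depends on observed data and can be missing at random. The rule also has an upper and a lower limit, so it gives no direction of bias, and the criteria say that participants may discontinue, not that they are removed. Drug changes, side effects and voluntary withdrawal between visits remain as reasons why the assumption could fail.

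**The result may be robust.** A reader might also infer that significance hangs entirely on the assumption. At the design values it does not: if missing PFM patients had the sham mean, an observed 5 mmHg would become 0.85 × 5 = 4.25 mmHg, with t = 4.25 / 1.99 = 2.13 and P about 0.035, still below 0.048. Nor does such dilution mean that the planned MMRM loses power. Completers would still differ by 5 mmHg, so the problem would be bias.

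**Auxiliary variables could make the imputation differ.** None are stated. They would make missing at random more plausible without testing departures from it.

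**The trial calls itself exploratory, supports retention and records reasons for leaving.** All true, and these lower the stakes, but they do not make the MCMC run a test of the assumption.

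**Conclusion.** The point holds in a limited form. Within this article, the named sensitivity analysis shares the primary analysis's missing-data assumption, so agreement between the two is not evidence of robustness to it. This rests on the standard form of both methods, since the article does not name the assumption itself. The primary analysis is not invalid for this reason. Data missing not at random are possible given the 15% allowance and the listed exits, but neither their presence nor the direction of any bias is established.

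On size: under the stated assumptions, an observed 5 mmHg effect survives until missing PFM values are about 7 mmHg worse than imputed, which exceeds the whole planned 5 mmHg benefit and is about half of one planned SD (7 / 13 = 0.54). That would be fairly reassuring, and less so for a smaller observed effect. The planned MCMC run would reveal neither.

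**What to change.** Keep the MCMC run as the starting point. Unless the full analysis plan already has an equivalent, add a delta-adjusted tipping-point analysis of the 1-month change in office SBP:

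- impute as planned;
- make the imputed PFM values progressively worse by delta;
- re-analyse at each step until the two-sided P exceeds the final alpha of 0.048;
- report that delta, so that readers can judge whether it is plausible.

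Fix this in writing before unblinding, and describe the MCMC result as a check under the same assumption.

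Imputing missing PFM values from the sham profile can be an optional extra scenario. It is debatable as a main one: PFM is a single procedure on day 0, so later drop-outs have already received it, and the documents give no basis for assuming that its effect vanishes.

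The cost is a few sentences and a little code in the SAS 9.4 already named, with no new data or visits. The downside is slightly more analysis work and possibly a less favourable robustness statement.

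### The interim rule enlarges the trial on the interim treatment comparison but keeps a final alpha of 0.048, which covers the interim look and not the data-driven sample size

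*Protocol article*

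**What the plan says.** All the elements stand in the second paragraph of Statistical method in the protocol article.

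- Timing: "An interim analysis is planned when 50 subjects (100 subjects in total) are enrolled in each group and completed 1 month follow-up".
- Efficacy stop: the trial is expected to end early "if the hypothesis test *P* value is less than the boundary value of the interim analyzed *α* for the primary endpoint".
- Otherwise, if P is above that boundary and power is low: "with statistical power less than 60%, re-estimating the sample size is needed to make the final statistical power greater than 80" per cent.
- Thresholds, attributed to O'Brien-Fleming: "the interim analyzed *α* = 0.005, and final *α* = 0.048".

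The first paragraph of the section names an MMRM adjusted for baseline office SBP as the primary analysis. It mentions no weighting by stage. Under Sample size, the PFM change "was expected to 10 mmHg with a deviation of 13 mmHg in the PFM group", against 5 mmHg with the same SD under sham. The design difference is therefore 5 mmHg, with 100 per group.

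**The concern.** An O'Brien-Fleming pair controls type I error when the total size is fixed in advance. Here the total depends on the interim comparison between the groups, and the final threshold stays the same.

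The direction of the adaptation matters. Raising the size only when conditional power is already about 50% or more does not inflate the ordinary pooled test. This rule raises it below 60% with no lower limit, so it covers the whole region where that test is unprotected.

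At stake is the 5% error rate of the only primary endpoint. There is also a practical matter. If power is computed at the observed effect, the rule asks for the largest enlargements when the interim result is least promising.

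**Working it through.** **Inputs.** From Statistical method: alphas 0.005 and 0.048, interim at 50 per group, trigger 60%, target 80%. From Sample size: 100 per group, SD 13, difference 5 mmHg. Assumed, because the article does not say: information fraction 50/100 = 0.5, ordinary pooled test at the end, and the caps shown below.

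**The plan's own figures.** The two-look O'Brien-Fleming boundary at fraction 0.5 gives 0.0052 and 0.0480, so the stated pair reproduces. With c1 = 2.807 and c2 = 1.977 and no change of size, overall two-sided error is 0.0499.

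**Conditional power.** Let n1 = 50, let n be the final size per group and n2 = n − n1, and let z1 = d / (13 × √(2/50)) = d / 2.6 for an interim difference d. For an assumed effect δ,

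CP = 1 − Φ{ (c2√n − z1√n1)/√n2 − (δ/13)√(n2/2) }.

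Example with d = δ = 3: z1 = 1.154. At n = 100 the argument is (19.77 − 8.16)/7.07 − 1.154 = 0.489, so CP = 0.31 and the rule fires. At n = 282 it is (33.21 − 8.16)/15.23 − 2.486 = −0.841, so CP = 0.80.

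**Trigger at the observed trend.** CP falls below 60% when z1 < 1.525, that is d < 1.525 × 2.6 = 3.96 mmHg. The probability of this is 0.35 when the true effect is 5 mmHg. Under the null it is 0.94 if zero and negative trends count, or 0.94 − 0.50 = 0.44 if only PFM-favouring trends do.

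**Why the pooled test loses protection.** Take d = 2, z1 = 0.769. Under the null, the chance of a final rejection in favour of PFM at n = 100 is 1 − Φ{(19.77 − 5.44)/7.07} = 1 − Φ(2.03) = 0.021. At n = 656, the size the rule asks for, it is 1 − Φ{(50.65 − 5.44)/24.62} = 1 − Φ(1.84) = 0.033. Enlarging raises the conditional error, and 0.048 makes no allowance for that.

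**Overall two-sided error**, by numerical integration over z1 under the null, pooled test at 0.048:

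| Cap per group | PFM-favouring trends enlarged | Either direction enlarged |
|---|---|---|
| No re-estimation | 0.0499 | 0.0499 |
| 150 | 0.054 | 0.057 |
| 200 | 0.055 | 0.061 |
| 400 | 0.058 | 0.067 |
| None | 0.061 | 0.072 |

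With power computed at the design effect of +5 mmHg, the total is about 0.054, and the PFM-favouring tail is 0.030 instead of 0.025.

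**Size required for 80%.** At the observed effect, differences of 3, 2 and 1 mmHg need 282, 656 and 2,671 per group, and no size gives power in favour of PFM at zero or below. At the design effect, the requirement stays under 300 per group for every interim result.

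**Sensitivity.** If 85 per group are evaluable (100 less 15% dropout), the fraction is 50/85 = 0.588. The error is 0.0494 without re-estimation, 0.062 or 0.075 uncapped (PFM-favouring or either direction), and 0.056 at the design effect.

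**Fixed-weight test.** With Z = √0.5·Z1 + √0.5·Z2, where Z2 uses stage 2 patients only, Z2 is standard normal under the null whatever n2 is chosen. Overall error stays at 0.0499 for any enlargement.

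**The case against.** The best defence is that the article never says how the two stages are combined. A threshold of 0.048 is also the right one for a weighted combination test, so the number fits a valid design. Combination method, cap and definition of power often sit in an analysis plan or committee charter, and neither is shown. The word unblinded does not appear either.

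Part of this stands. The missing cap and definition of power are not faults in themselves, and the pooled test is an inference. It is the natural one, since the section names an MMRM with no weighting. Tying the trigger to the between-group P value likewise makes a blinded, SD-only re-estimate a poor fit to the text. What the article does fix is an enlargement rule with no lower limit and a final alpha that takes no account of it.

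The Trial design section calls the trial exploratory. That lowers the stakes, but the plan still claims O'Brien-Fleming control and an efficacy stop.

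A reader might infer stronger versions that the documents do not support:

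- *The error is 0.072 as written.* That needs the trial to be enlarged when sham looks better, which nothing in Outcomes or Statistical method suggests.
- *The error at the design effect is 0.059.* That needs the sign of the 5 mmHg effect to be reversed whenever the interim trend is negative.
- *The rule has no workable size.* This holds only if power is taken at the observed effect.
- *The 0.048 is unadjusted, and enlargement follows whenever power is low.* It is adjusted for the look, and P must also exceed 0.005.

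**Conclusion.** The concern holds in this limited form. Read as effect-based re-estimation with an ordinary pooled final test, the stated rule does not keep the 5% level. On the more plausible readings (planned 100 per group, enlargement aimed at showing a benefit of PFM), the two-sided error is about 0.054 to 0.061 instead of 0.0499. It reaches 0.072 only if sham-favouring trends are also enlarged.

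This is moderate inflation of the sole primary test. It rests on three assumptions: the interim comparison drives the new size, the stages are pooled without fixed weights, and low conditional power does not stop the enlargement. The rule is likely to come into play: at the observed trend it fires with probability 0.35 even if the design effect is true. It should be corrected in wording before the interim.

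**What to change.** Keep the re-estimation rule and add the following to the protocol or analysis plan before the interim data are seen.

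1. The final test is the Cui-Hung-Wang combination Z = √0.5·Z1 + √0.5·Z2, with weights fixed from the planned information and each statistic taken from its own stage's patients, tested two-sided at 0.048.
2. A stated maximum sample size.
3. A conditional-power floor below which the size is not raised.
4. A statement that the power in the rule is conditional power, and at which effect it is computed.

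The cost is wording plus a small loss of efficiency if the size is raised, because stage 2 patients then count for less than their number. A capped, blinded re-estimate of the SD would also avoid most of the inflation, but it is a different design and a matter of preference.

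Trial status reports 74 participants recruited by 8 February 2022, fewer than the 100 the interim needs. Whether the interim has since taken place cannot be told from the article. Once the interim comparison has been seen, the change is no longer prespecified.
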